### Eligibility criteria {10}

#### Inclusion criteria

##### Gastrointestinal tumors:

Patients aged 18 years or older, with no upper age limit.Histological diagnosis of gastrointestinal cancer, including stomach, colon, bile ducts, and pancreas.Measurable disease confirmed by diagnostic tests and planned to receive chemotherapy as the primary treatment.Presence of at least one discrete metastatic site identified by CT scan of the chest and/or abdomen and/or bone scintigraphy.ECOG performance status of 0 to 2, with a life expectancy greater than 2 months.Ability to swallow and retain oral medication, and absence of uncontrolled emesis or persistent diarrhea.Adequate renal, hepatic, and cardiac function defined as follows:Renal Function: Glomerular filtration rates greater than 30 mL/min, determined by blood chemistry (CKD-EPI calculation) and/or urinary creatinine clearance and/or Glomerular filtration scintigraphy.Liver Function: Alkaline phosphatase, ALT, and AST should not exceed 5 times the reference value according to laboratory technique. Bilirubin should not exceed 3 times the reference value.Cardiac Function: Echocardiogram and/or electrocardiogram results should indicate no untreated or decompensated heart failure, with an ejection fraction greater than or equal to 50%. Additionally, any value lower than the mentioned threshold, posing a risk to the patient, should be assessed by the investigator.Female patients of childbearing age who are not using safe non-hormonal contraceptive methods must undergo a negative pregnancy test prior to screening.Fertile female subjects (not postmenopausal for at least 12 months or surgically sterile) and their male partners must use one of the following contraceptive methods from study entry, throughout the study, and for at least 6 months after using Esperanza extract (unknown effects on the developing fetus):Complete abstinence from sexual intercourse, beginning at least one complete menstrual cycle before study drug administration (note: sexual abstinence as a contraceptive method should be limited to cases where it is already an established choice of the patient's pre-existing lifestyle).Vasectomy in the partner of a female subject.Intrauterine device (IUD).Double barrier method (condom, contraceptive sponge, diaphragm, or vaginal ring with spermicidal jelly or cream).Willingness to complete the study and comply with follow-up interventions.

#### Exclusion criteria

Subjects meeting any of the following conditions are ineligible for participation in this study:Individuals who have received treatment as part of any other therapeutic clinical protocol within the 30 days preceding study entry or during the course of the study.Patients currently receiving other investigational agents.Female subjects who are pregnant or lactating. Confirmation of non-pregnancy must be established through a negative result on a serum or urine pregnancy test conducted during the screening process. Postmenopausal or surgically sterilized women are exempt from undergoing pregnancy tests.Individuals with serious concomitant morbidities that are active as determined by the investigator, including:Untreated or uncontrolled arterial hypertension, or values consistently above 140/90 mmHg despite treatment.Untreated or decompensated heart failure according to the Stevenson scale.Coronary artery disease without intervention, confirmed by catheterization, or symptomatic angina.Clinically or electromyographically documented neuropathy.Liver cirrhosis/hepatic dysfunction without treatment or values that meet the exclusion criteria.Chronic kidney disease with a glomerular filtration rate (GFR) less than 30 ml/min.Untreated or decompensated autoimmune diseases.Diabetes without treatment or with HbA1c levels greater than 8% despite treatment.Dyslipidemia without treatment or with triglyceride values greater than 300 or LDL levels greater than 200 despite treatment.Synchronous or metachronous active tumors (hematological or solid) within the 2-year period prior to study entry.Any other concomitant disease, not mentioned above, that, in the investigator's opinion, poses a risk to the patient and is not a suitable substitute.Subjects with a confirmed diagnosis of HIV prior to enrollment or a positive HIV diagnosis at the time of screening.Patients who have undergone solid organ transplants.Any other condition, as determined by the principal investigator, that renders the subject ineligible to participate in this study.

### Who will take informed consent? {26a}

The informed consent process will be conducted by the principal investigator or a designated representative. They will thoroughly explain the study's objectives, procedures, and the potential benefits and risks of participation to each prospective patient. Prior to undergoing any study-related procedures or discontinuing any prohibited medication, every patient or their legally acceptable representative must sign and date the informed consent form approved by the Institutional Review Board (IRB).

### Additional consent provisions for collection and use of participant data and biological specimens {26b}

N/a: The collection of all data and biological samples for this study is an integral part of the protocol activities.

## Interventions

### Explanation for the choice of comparators {6b}

In Phase Ib, no comparator will be used as the primary objective is to determine the maximum tolerated dose (MDT) in gastric tumors and acute leukemias. In Phase II, a placebo group will be included for gastric tumors, while both groups will receive the standard chemotherapy for their respective underlying diseases. However, for acute leukemias, a comparison will be made with a cohort of historical records from the hospital where the relevant clinical outcomes have already been established, considering the causal factors.

### Intervention description {11a}

#### Phase I treatment:

Patients who meet the inclusion criteria and have metastatic gastrointestinal tumors (colon, pancreas, stomach, and bile ducts) or newly diagnosed acute leukemias will initiate treatment with 1000 mg of Esperanza extract daily, divided into two doses of 500 mg, for a duration of 4 weeks. In the event of toxicity, the dose level will be adjusted accordingly. If toxicity occurs, the next dose level will be reduced to 500 mg using the same dosing schedule, and if there is no toxicity after 4 weeks, the dose will be increased to 2000 mg. This dose adjustment will be conducted with the same group of patients, both for escalation and de-escalation, who have completed the previous dose level, ensuring a total treatment duration of 8 weeks. The administration of the phytomedicine Esperanza will continue throughout the intervention period, without interruption, for the entire 8-week treatment duration, unless there is clinically significant toxicity that meets the investigator's criteria for discontinuing the intervention. Table 1 provides a comprehensive list of the activities to be carried out during the patients' intervention.

**Table 1 Tab1:** Schedule of activities for phase ib to evaluate safety and MTD in gastrointestinal tumors and acute leukemias

Schedule of activities				
	**Enrollment**	**Initial Visit and chemotherapy cycle 1**	**Cycle 2**	**Close-out**
**Time point**	**Week 1**	**Week 2**	**Week 6**	**Week 7**
Enrolment				
Screening and Informed Consent	X			
Physical Examen		X	X	X
Clinical Record		X	X	X
HIV Test and Pregnancy test	X			

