**Methods:**

This is a prospective, open label, phase I/ randomized, double-blind single-center phase II study designed to evaluate the safety and efficacy of Esperanza extract in patients with metastatic gastrointestinal tumors and acute leukemias. In stage 1, the study will determine the MTD and assess safety. In stage 2, safety at the MTD will be evaluated, and the efficacy of Esperanza extract will be explored in both metastatic gastric tumors and acute leukemias. Quality of life improvement will be the primary outcome in the gastric tumor group, while different efficacy outcomes will be assessed in the acute leukemia group. A placebo group will be used for comparison in the gastric tumor group, and a historical control group will be used in the acute leukemia arm.

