### Objectives {7}

The main goal of phase I is to assess the safety, toxicity, and maximum tolerated dose (MTD) of the Esperanza extract in patients diagnosed with metastatic gastric tumors and acute leukemias. In phase II, the focus shifts to evaluating the safety of the extract and examining its impact on improving patients' quality of life using the QLQ-C30 scale for gastric tumors. Additionally, in the context of acute leukemias during phase II, the emphasis remains on determining the safety of the extract and investigating its potential to enhance the rate of remission during induction therapy and/or facilitate hematological recovery.

In addition to the primary objectives, there are important secondary objectives for gastric tumors. One of these is to evaluate the influence of the Esperanza extract on progression-free survival and clinical response, which will be assessed using the RECIST 1.1 criteria. For acute leukemias, the assessment will focus on event-free survival, defined as the duration from enrolment to disease progression, including local or distant recurrence, second primary malignancy, primary malignancy-related death, or death from any cause, whichever comes first. Furthermore, a thorough evaluation of the impact on patients' quality of life will also be conducted.

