### Trial design {8}

This is a comprehensive phase I/II clinical study designed to assess both the safety and efficacy of the Esperanza extract in treating gastric tumors and acute leukemias. The study consists of two phases: Phase I is an open-label study that involves dose escalation to determine the MTD of the extract (Fig. 1). In Phase II, specifically for gastric tumors, a double-blind, randomized, placebo-controlled approach will be employed. Participants will be divided into two groups, with both groups receiving standard chemotherapy in combination with either the Esperanza phytomedicine or a placebo (Fig. 2a).

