**Fig. 2 Fig2:**
[figure not shown]
Comprehensive Flow Diagram for Phase II PA001 Trial **a**) Gastrointestinal Tumors, **b**) New diagnosis Acute Leukemias, and **c**) Relapsed Acute Leukemias

Conversely, in the acute leukemia group, the MTD will be administered to patients during the induction cycle. The results from these acute leukemia cohorts will be compared to a historical cohort at the hospital, allowing for further analysis and evaluation (Fig. 2b). In relapse acute leukemia patients, the MTD will be administered to patients during the rescue cycles 1 to 3, the results will be compared to a historical cohort at the hospital (Fig. 2c).

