### Participant timeline {13}

#### Sample size {14}

For phase I, a sample size of 6 patients was determined for gastric tumors and acute leukemias. In case of presentation of any adverse event in the first in these patients, the dose will be decreased for the second cycle; in case of an adequate safety profile, the dose will be doubled for the second cycle.

The sample sizes for phase II were determined for both gastrointestinal tumors and hematologic tumors. For gastrointestinal tumors, a sample size of 30 patients was calculated, with 15 patients per group, considering a mean difference of at least 6 points in quality of life, a standard deviation of 5 and 6 points for each group, an alpha error of 0.05, and a beta error of 0.20. Additionally, a 10% allowance was added for possible study losses. For hematologic tumors, the sample size calculation was based on response criteria such as improvement, remission rate, and hematologic recovery. The ANOVA test was used, an alpha error of 0.05, a beta error of 0.20, and an effect size of 0.4. The resulting sample size was 28.

It should be noted that these sample sizes will be reassessed at the end of phase I for both gastric tumors and acute leukemia. The recalculated sample size for phase I/II is 36 for gastrointestinal tumors and 46 for hematologic tumors.

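### Phase I makes one dose change, so it cannot support an MTD in two of its four outcomes, and Table 1 closes out about one week into the second 4-week dose level

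*Protocol article*

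**What the plan says.** The dose rule is in Intervention description {11a}, Phase I treatment. Patients start at 1000 mg daily for 4 weeks. After toxicity the next level is 500 mg; otherwise, "if there is no toxicity after 4 weeks, the dose will be increased to 2000 mg". The change is made in the same patients, "both for escalation and de-escalation, who have completed the previous dose level, ensuring a total treatment duration of 8 weeks". Sample size {14} sets 6 patients for phase I and repeats the single change: the dose is lowered for the second cycle after an adverse event, and "in case of an adequate safety profile, the dose will be doubled for the second cycle".

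The article makes the MTD the product of this phase:
- Abstract, Methods: "In stage 1, the study will determine the MTD and assess safety. In stage 2, safety at the MTD will be evaluated".
- Objectives {7}: "The main goal of phase I is to assess the safety, toxicity, and maximum tolerated dose (MTD) of the Esperanza extract".
- Trial design {8}: "Phase I is an open-label study that involves dose escalation to determine the MTD of the extract".
- Explanation for the choice of comparators {6b}: "the primary objective is to determine the maximum tolerated dose (MDT) in gastric tumors and acute leukemias".

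Phase II then uses it. For newly diagnosed leukaemia, Trial design {8} says that "the MTD will be administered to patients during the induction cycle". Phase II treatment doses both the gastrointestinal and the leukaemia patients at the MTD as already determined.

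Table 1, the phase I schedule, puts the initial visit with cycle 1 in week 2, cycle 2 in week 6 and close-out in week 7. The safety laboratory tests and electrocardiogram are scheduled at these three visits.

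**The concern.** An MTD needs a tolerated level and evidence that the next level up is not tolerated. With one change from a middle dose, only some outcomes give that pair. In the others the stated phase I result does not exist, and the article words phase II as if it always will.

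The two failing outcomes differ in weight. If 2000 mg is tolerated, it may be a reasonable dose to carry forward, and the error lies only in calling it an MTD. If 500 mg is toxic, phase II has no dose, and whether it opens is left implicit.

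The schedule affects every outcome. The second level decides the phase II dose. If its last scheduled laboratory tests come about one week in, it is judged on less laboratory follow-up than the first level had, and a toxicity that appears in the laboratory after that week could be missed before the dose is fixed.

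**Working it through.** **1. Number of levels.** Inputs from Phase I treatment: 8 weeks in total, 4 weeks per level. 8 / 4 = 2 levels, hence 2 − 1 = 1 dose change. This agrees with Sample size {14}, where the only change is at the second cycle.

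**2. Outcomes,** reading the rule as one decision for the whole group:

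| First level | Second level | What is shown |
|---|---|---|
| 1000 mg tolerated | 2000 mg toxic | MTD 1000 mg |
| 1000 mg toxic | 500 mg tolerated | MTD 500 mg |
| 1000 mg tolerated | 2000 mg tolerated | No upper bound; MTD not reached |
| 1000 mg toxic | 500 mg toxic | No tolerated dose |

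Two of the four outcomes do not locate an MTD. If doses are changed patient by patient there are more patterns, but both unlocated ends remain.

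**3. Schedule.** Dosing starts in week 2, so the first level covers weeks 2 to 5. The second starts in week 6 and covers weeks 6 to 9, ending at about week 10 (6 + 4). Table 1 closes out in week 7: 7 − 6 = 1 week into the second level, about a quarter of its 4 weeks, and 10 − 7 = 3 weeks before its end. Table 3, for phase II leukaemia, uses the same week 2 and week 6 visits and puts close-out in week 10, which is the spacing that the 8-week rule implies.

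**4. What the article provides at the end of phase I.** Interim analyses {21b} covers a safety review, possible added safety measures in phase II and a recalculated sample size. Criteria for discontinuing {11b} covers withdrawal of individuals. Neither addresses a phase I without a tolerated dose.

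**5. Illustration only.** The article gives no toxicity rates. Assume per-patient rates at 500/1000/2000 mg, 6 patients, a level called toxic when at least k patients have toxicity, independent periods, and all six continuing. With q(p) = P(at most k − 1 of 6):

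P(MTD not reached) = q(1000) × q(2000); P(no tolerated dose) = (1 − q(1000)) × (1 − q(500)).

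Example, rates 5/10/20% and k = 1: q(500) = 0.95^6 = 0.735, q(1000) = 0.90^6 = 0.531, q(2000) = 0.80^6 = 0.262. This gives 0.531 × 0.262 = 0.139 and 0.469 × 0.265 = 0.124.

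| Assumed rates (%) | MTD not reached, k=1 / k=2 | No tolerated dose, k=1 / k=2 |
|---|---|---|
| 2/5/10 | 0.391 / 0.857 | 0.030 / 0.0002 |
| 5/10/20 | 0.139 / 0.580 | 0.124 / 0.004 |
| 10/20/35 | 0.020 / 0.209 | 0.346 / 0.039 |
| 20/35/50 | 0.001 / 0.035 | 0.682 / 0.235 |

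Within-patient correlation of 0.5, or withdrawal of patients with toxicity at 1000 mg, changes the figures but not the picture. Over all these settings the chance of no tolerated dose runs from below 0.1% to 70%. That spread comes from the assumptions.

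**6. Check on the fix.** Suppose doses change patient by patient and the rule takes simply the highest level that did not meet the trigger. It could then pick 2000 mg although 1000 mg met the trigger, because only patients who tolerated 1000 mg receive 2000 mg. With k = 1, independent periods, and rates p at 1000 mg and r at 2000 mg, the chance is

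(p + (1−p)(1−r))^6 − ((1−p)(1−r))^6 − p^6.

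For p = 0.10 and r = 0.20: 0.82^6 − 0.72^6 − 0.10^6 = 0.304 − 0.139 − 0.000 = 0.165. For the four sets of rates it is 16, 16, 12 and 9%. The selection rule therefore needs a guard.

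**The case against.** Any finite set of doses can end with all levels tolerated or none, and more levels only move the two ends. This stands: the fix proposed here does not locate the MTD in those outcomes either. It limits the claim to what was shown.

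If the full protocol defines the MTD as the highest tested dose that is tolerated, the both-tolerated outcome yields 2000 mg by definition. That makes this half mainly a matter of claim. Fig. 1 and the full protocol are not available, so a reader might infer that the trial has no rule for declaring the MTD. The article does not show that, and the absence of such a rule is not the point made here.

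In the both-toxic outcome, a reader might infer that phase II would go ahead at a toxic dose. The text does not say so. Phase II is given at a determined MTD; without one there is no dose to give, and a safety analysis lies between the phases. An explicit no-go clause may stand in the full protocol, so this half rests partly on the silence of a condensed article.

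On the schedule, a reader might infer that nobody is observed after week 7. That is also not supported. The article provides weekly telephone contact, adverse-event monitoring throughout the study and one month of follow-up after treatment. None of these is a scheduled laboratory test, so the conflict between Table 1 and the 8-week rule stands.

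**Conclusion.** The point holds, with minor to moderate weight. Two levels and one dose change cannot support an MTD claim if 1000 and 2000 mg are both tolerated, and give no phase II dose if 1000 and 500 mg are both toxic. Both follow from the stated rule without any outside figure. The week 7 close-out contradicts the 8-week treatment rule and leaves the last scheduled laboratory tests about one week into the second level.

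The outcome probabilities rest wholly on assumed toxicity rates, triggers and correlation. They show that neither failing outcome can be dismissed, but they do not estimate this trial's risk of ending without an MTD and should not be quoted as if they did.

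**What to change.** 1. In Table 1, move the existing close-out visit from week 7 to the end of the second level, about week 10. Judge that level by the same toxicity criterion over the same 4 weeks as the first before the phase II dose is chosen.
2. Wherever the article names the MTD as the phase I output or the phase II dose, use recommended phase II dose instead. Define it as the highest tested level that did not meet the toxicity trigger, provided no lower tested level met it. If 2000 mg is tolerated, report that the MTD was not reached.
3. In Interim analyses {21b}, state that phase II does not open at a tested dose if no tested level is tolerated.

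The toxicity criterion itself remains for the investigators to set.

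Cost: phase I close-out about 3 weeks later, a weaker phase I claim, and a phase II that no longer opens automatically. No more patients and no new visit are needed.

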**Efficacy Assessment**					
RECIST		X			X
Tumor Antigens		X			X
CA199		X			X
ACE		X			X
Metabolome		X		X	X
Microbiome Analysis		X			X
Proinflammatory Cytokines		X		X	X
Circulating DNA		X		X	X
Ketone Bodies		X		X	X
Tumor Infiltration		X			X
QLQ C-30 Quality of Life Surveys		X	X	X	X
Progression-Free Survival		X			X

For newly diagnosed acute leukemias, a total of 28 new patients will be recruited, and an additional six patients will be recruited for the relapsed leukemias group. Both groups will receive continuous treatment with the Esperanza extract at the determined MTD for four weeks. Standard chemotherapy treatment for their underlying disease will be administered to both groups. At the end of the treatment cycle, safety and efficacy evaluations will be conducted. Table 3 provides a comprehensive list of the activities to be carried out during the patients' intervention.

**Table 3 Tab3:** Activity schedule for phase II clinical trial in acute leukemias

Schedule of activities				

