**Efficacy Assessment**				
Myelogram and flow cytometry		X		X
Tumor Antigens		X		X
Metabolome		X		X
Microbiome Analysis		X		X
Proinflammatory Cytokines		X		X
Circulating DNA		X		X
Ketone Bodies		X		X
Tumor Infiltration		X		X
QLQ C-30 Quality of Life Surveys		X	X	X
Progression-Free Survival		X		X

^a^For new diagnosis the intervention will be only in induction chemotherapy cycle with the close out visit in week 6

The Esperanza and Placebo capsules will be manufactured at Labfarve Laboratories in strict adherence to Good Manufacturing Practices (GMP) conditions. The Esperanza capsules contain 500 mg of *P. alliacea* extract, which is obtained from freshly crushed leaves infused with purified water. The extraction process has a DER (Drug extraction ratio) of 29–44:1, and the hexose content ranges between 3.0% and 5.0%. Each batch undergoes chemical profile assessment to ensure consistency. Quality controls are conducted in accordance with regulations set forth by the World Health Organization (WHO), the National Institute for Food and Drug Surveillance (INVIMA), and the U.S. Food and Drug Administration (FDA). These controls will be applied to both the investigational phytomedicine and the placebo, guaranteeing an identical physical appearance and a shelf life of six months from the date of manufacture.

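### Table 1 schedules the last phase I safety tests about one week into a four-week second dose level; and if 2000 mg is chosen, phase I will hold no planned induction data at that dose

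*Protocol article*

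**What the plan says.** The Phase I treatment section starts patients with metastatic gastrointestinal tumours or newly diagnosed acute leukaemia on 1000 mg daily for four weeks. Toxicity leads to 500 mg at the next level. Otherwise, "if there is no toxicity after 4 weeks, the dose will be increased to 2000 mg". No new cohort is opened for the second level: "This dose adjustment will be conducted with the same group of patients, both for escalation and de-escalation, who have completed the previous dose level". Sample size {14} ties the change to the chemotherapy cycle: "in case of an adequate safety profile, the dose will be doubled for the second cycle". Total treatment is 8 weeks, given "without interruption, for the entire 8-week treatment duration".

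Table 1 (phase I schedule) has the initial visit with chemotherapy cycle 1 in week 2, cycle 2 in week 6 and close-out in week 7. Drug dispensing and the laboratory panel are marked at those three visits only.

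For phase II, Trial design {8} states that "in the acute leukemia group, the MTD will be administered to patients during the induction cycle". The footnote to Table 3 adds: "For new diagnosis the intervention will be only in induction chemotherapy cycle with the close out visit in week 6". The Phase II treatment section sets the number of newly diagnosed leukaemia patients at 28.

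**The concern.** Phase I exists to supply the dose for phase II, and two features weaken what it can say about the second dose level.

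First, the schedule and the text disagree. If the last panel is drawn in week 7 while dosing runs to about week 10, laboratory toxicity that takes more than a week or so to appear after the dose change has no scheduled test to catch it. This holds whichever way the dose moved.

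Second, the dose is tied to the cycle by design: 1000 mg goes with cycle 1, and any other dose goes with cycle 2. If 2000 mg becomes the phase II dose, it will have been observed only in patients who had already completed four weeks at 1000 mg. It would then be started without run-in in newly diagnosed leukaemia patients during induction, the one setting in which phase I did not plan to give it.

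**Working it through.** **Inputs.** First dispensing in week 2, cycle 2 in week 6, close-out in week 7 (Table 1). Each level lasts 4 weeks and total treatment 8 weeks (Phase I treatment). The dose changes for the second cycle (Sample size {14}). There are 28 newly diagnosed phase II leukaemia patients (Phase II treatment), treated in induction only (Table 3 footnote).

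**The plan's own figure.** 4 weeks at the first level + 4 weeks at the second = 8 weeks, as stated.

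**Calendar.**
- Dose change: week 2 + 4 = week 6, which matches the Table 1 cycle 2 visit.
- End of treatment: week 2 + 8 = week 10.
- Last scheduled panel: week 7.
- Second level covered by scheduled tests: 7 − 6 = 1 of 4 weeks.
- Second level after the last scheduled test: 10 − 7 = 3 weeks.
- Whole treatment period covered: 7 − 2 = 5 of 8 weeks.

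**Precision.** Visits are labelled by week, not by day. From the last day of week 6 to the first day of week 7 is 1 day; from the first day of week 6 to the last day of week 7 is 13 days. Of the 28 days at the second level, 28 − 13 = 15 to 28 − 1 = 27 days follow the last panel. About 3 weeks is the nominal value.

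**Comparison with the other schedules.** Tables 2 and 3 also have cycle 2 in week 6, and both place the next visit in week 10 (cycle 3 in Table 2, close-out in Table 3). Only Table 1 has week 7.

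**Dose by cycle in phase I.**

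| Dose carried forward | Planned phase I exposure in cycle 1 / induction | Gap for phase II induction |
|---|---|---|
| 500 mg | None, but twice that dose was given in cycle 1 | No comparable safety gap |
| 1000 mg | Yes, the starting dose | None |
| 2000 mg | None | Yes, for the 28 newly diagnosed patients |

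The Acute Leukemias eligibility criteria tie induction to the first treatment cycle, so cycle 1 and induction coincide for phase I leukaemia patients. The zero in the last row holds whether the dose rule is applied per patient or to the group, and whether the stated 6 patients are per tumour type or in total. One unplanned exception is possible: a patient refractory to cycle 1 might be re-induced in cycle 2. The gap matters less for gastrointestinal tumours, because their three phase II cycles include cycle 2.

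**The case against.** The week-7 entry may well be a slip. The text states 8 weeks of treatment twice, and the other two tables use week 10. Laboratory follow-up is also not absent: Adverse event reporting and harms {22} calls for clinical and laboratory monitoring throughout the study, patients are telephoned weekly, and they are followed for a month after treatment. This stands as a limit on the size of the problem. A reader might infer that patients go unmonitored for three weeks, and the protocol does not support that. What is missing is a dated panel in weeks 8 to 10, and none of these provisions supplies one. A slip in the schedule still needs correcting, because staff will follow the table.

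On induction, within-patient escalation is an open design choice, 2000 mg would still be observed alongside chemotherapy, and phase II is itself a safety stage. Interim analyses {21b} allows extra safety measures to be added first. Moreover, the 2000 mg branch may be hard to reach. Sample size {14} lowers the dose after any adverse event in the first cycle, with no restriction to severe or extract-related events, in patients who are on chemotherapy. All of this stands. A reader might infer that 28 patients will be started on an untested dose. That does not follow: the gap arises only if 2000 mg is chosen, and the dose would have been tested, though not in induction. These points make the second part a matter of how the result is described, not a reason to reject the escalation design.

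**Conclusion.** The schedule error holds as printed. Table 1 ends scheduled safety testing about one week (1 to 13 days) after the dose change and leaves about 3 of 4 weeks at the second level without a scheduled panel. This assumes that dosing starts at the week-2 visit and that the 8-week duration in the text is the intended one.

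The induction point holds conditionally. If 2000 mg is carried forward, planned phase I exposure to it in cycle 1 or induction is zero, and the 28 newly diagnosed phase II leukaemia patients would receive it only there. If 1000 mg is carried forward there is no such gap, and at 500 mg there is no comparable one.

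Both are modest corrections to the schedule and to the phase I claim. They do not show that phase I cannot inform phase II. The protocol also describes the duration of relapsed-leukaemia dosing inconsistently. That is a separate matter, since phase I enrols only newly diagnosed leukaemia, and it is not relied on here.

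**What to change.** 1. In Table 1, move close-out and its safety tests to the end of the 8-week treatment, about week 10, in line with the week-10 visit in Table 3.
2. In the safety analysis already planned at the end of phase I (Interim analyses {21b}), tabulate toxicity by dose and cycle together. Describe a 2000 mg result as tolerated in cycle 2 after four weeks at 1000 mg, not as an MTD established in induction.

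The cost is one phase I visit about three weeks later and a narrower phase I claim. No patients or phase II visits are added, and phase II blinding is untouched. If dosing does run to about week 10, the safety data for the second level could not be complete sooner in any case.

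A formal rule that reverts the dose after the first few phase II induction patients is not proposed. It would operate inside phase II, so it would supply no induction data beforehand, and a reversion would split the leukaemia cohort across two doses in the comparison with historical controls. The choice of dose stays with the sponsor and investigators.
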